### Patient Identification and Recruitment

Cluster trials are vulnerable to selection bias through systematic differences in referral behaviour between experimental and control practices. We will minimise this potential bias by recruiting patients through searching GP records, rather than by direct GP referral. This method was also the most productive when we tested a range of recruitment methods in our pilot trial [17]. We will identify suitable patients by examining electronic case records for all patients in each general practice. The search will be limited to patients seen by their GPs in the previous four weeks who have been allocated a 'Read Code' for depression, and will be conducted by practice staff or Clinical Studies Officers blind to the random allocation of the GP surgery.

Identified patients will receive a letter from their GP surgery inviting them to take part in the study, enclosing a patient summary sheet outlining the study with a 'Permission for researcher to contact' form to allow a researcher to contact them. Recruitment which requires patients to return paper forms is known to have a very poor response rate, typically only 15% of those contacted will agree to be contacted, a threat to the study's external validity. A recent review of RCT recruitment methods [26] showed that the only likely method of improving recruitment was through telephone reminders by clinicians to non-responders. Consequently, in order to make our sample more representative of a primary care depressed population, we will attempt to enhance our response rate through telephone follow up by practice staff or Clinical Studies Officers.

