### Allocation

Once the baseline assessments are complete, the participant's details will be entered into our automated allocation service via telephone or the internet. Each participant will be assigned an ID number and if their practice is one assigned to collaborative care then the participant's details will be automatically sent to the relevant case manager to alert them to contact this person. All new participants' details are also sent to the trial coordinator and their GP will be informed of their involvement in the study.

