## Intervention - Case Management

The experimental intervention will follow the criteria identified by Gunn et al [9] for effective quality improvement strategies, which we have developed into a collaborative care protocol, tailored to UK systems and incorporating the preferences of patients, specialists and GPs from our trial platform [17,20].

Participants will receive a structured management plan including education about depression, medication management, behavioural activation and relapse prevention. The case manager will reinforce the information given to participants by their GP and by helping participants and GPs problem solve any difficulties with medication concordance, enabling participants to make good use of their medicines. Behavioural Activation (BA) is an effective cognitive-behavioural treatment of depression [27] that focuses upon reducing avoidance and increasing activity. We found BA to be acceptable in our pilot trial [20]. Relapse prevention will involve the development of individualised recovery plans which will help participants identify signature alert symptoms to prompt them to consider reinstating both their pharmacological and psychological depression management strategies.

Scheduled patient follow-ups will be organised via six to twelve scheduled telephone and face-to-face contacts by case managers with participants over a period of fourteen weeks. After an initial face-to-face contact most other contacts will be by telephone, although the option for further face-to-face contacts will be available for participants who are having difficulty settling to telephone contact. Negotiation of contact frequency will take into account participant preference, response to treatment, the requirements of the psychosocial support programme and the amount of GP-patient contact. However, in general, contacts will be weekly for the first five weeks of contact, followed by fortnightly thereafter. The initial contact session will be 30-40 minutes with subsequent sessions 15-20 minutes each.

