## Informing potential participants of possible benefits and known risks

The patient information leaflets will provide potential participants with information about the possible benefits and any known risks of taking part in the trial. Participants will be given the opportunity to discuss this issue with either their GP or trial coordinator prior to consenting to participate. The trial coordinator will inform the participants if new information comes to light that may affect the participants' willingness to participate in the trial.

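### A randomised practice's own staff may search records and telephone non-responders, but their blinding to allocation cannot credibly last in intervention practices and is not stated at all for the calls

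*Protocol article*

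**What the plan says.** The section on patient identification and recruitment opens with the threat: "Cluster trials are vulnerable to selection bias through systematic differences in referral behaviour between experimental and control practices". Its answer is to find patients through GP records instead of GP referral. The search rule is mostly objective: "The search will be limited to patients seen by their GPs in the previous four weeks who have been allocated a 'Read Code' for depression". The search "will be conducted by practice staff or Clinical Studies Officers blind to the random allocation of the GP surgery".

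Reply to postal invitations is expected to be poor, so "we will attempt to enhance our response rate through telephone follow up by practice staff or Clinical Studies Officers". No blinding is mentioned for this step.

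Under Allocation, the practice's assignment already exists when a participant is entered: "if their practice is one assigned to collaborative care then the participant's details will be automatically sent to the relevant case manager". For every participant, in either arm, "their GP will be informed of their involvement in the study". The case management section has the case manager working with the practice's doctors as well as its patients, "by helping participants and GPs problem solve any difficulties with medication concordance". The abstract lists better communication between specialists and GPs as part of the intervention.

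**The concern.** In a cluster trial that recruits patients after the clusters are allocated, randomisation protects the comparison of practices. It protects the comparison of patients only if recruitment does not depend on the arm. The plan recognises this and relies on a blinded search. Yet one of the two groups allowed to search, and later to telephone, works inside the randomised unit.

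Staff who know that their practice offers collaborative care may call some non-responders and not others, or describe the study more warmly, without any intent to distort. The arms could then differ in prognosis. Minimisation balances practices on centre, deprivation and size, not the patients who later join. The primary analysis adjusts for baseline depression score, which would not remove differences in motivation, chronicity or treatment preference. A bias of this kind does not shrink as the sample grows.

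**Working it through.** The point is procedural, and the plan gives no figure to reproduce. The statements are set side by side first; simple arithmetic then shows how much recruitment could be exposed.

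**Step 1: who is blind, and at which step.**
- Record search: practice staff or Clinical Studies Officers. The word *blind* can be read as covering both groups or only the Officers. On the first reading, staff are said not to know their own practice's arm. On the second, no blinding of practice staff is claimed.
- Telephone follow-up: the same two groups, with no statement on blinding.

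**Step 2: what reaches the practice.**
- Both arms: the GP learns that the patient is in the study. Allocation is not mentioned.
- Intervention arm only: a case manager contacts the patient, helps GPs with medication problems and is part of closer links with specialists.
- The Study Design section justifies cluster allocation by organisational effects that may reach patients in the same practice who do not receive the patient-level intervention. That argument is hard to combine with staff of the practice staying unaware of the intervention.

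**Step 3: how much recruitment could follow the start of case management.** Inputs: 550 patients (Sample Size), 48 practices (Recruitment of GP practices), 18 months of recruitment (Forecast execution dates), 15% typical reply to paper forms (Patient Identification and Recruitment).
- Recruits per practice: 550 / 48 = 11.5.
- Recruits after their practice's first: 550 − 48 = 502, or 502 / 550 = 91%. This covers both arms. With an equal split (assumed: 24 practices and 275 patients per arm), the intervention arm contributes 275 − 24 = 251. That is an upper limit, because patients found in the same search as the first recruit may join before staff learn anything.
- Invitations at a 15% reply: 550 / 0.15 = 3,667, or 3,667 / 48 = 76 per practice. This is a minimum at that reply rate, since it treats everyone who agrees to contact as eligible and enrolled. With a four-week search window, repeated searches are likely, though the article does not say so.

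**Step 4: weight of the telephone step.** If letters yield 15% and calls raise the total to *r*, the share of agreeing patients who come through a call is (*r* − 0.15) / *r*. The article gives no *r*, so these values are assumptions:

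| Total response *r* | Invitations per practice, 550 / *r* / 48 | Share through a call |
|---|---|---|
| 30% | 38 | 0.15 / 0.30 = 50% |
| 50% | 23 | 0.35 / 0.50 = 70% |

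If the calls work as hoped, a large part of the sample could enter through the step with no stated blinding.

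**Step 5: existing safeguards.** The Read-code rule fixes who is on the list. The CIS-R, administered by a researcher, confirms that those who come forward are depressed. Neither determines who on the list is called or what is said to them.

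**The case against.** The strongest reply is that the text never says practice staff learn the arm. The GP is told of involvement, not allocation; the alert goes to the case manager; the searchers may not be the treating GPs; and control practices could at most infer their arm. This stands against the stronger reading a reader might draw, that blinding becomes impossible after the first participant. The documents support only that it is not credible or sustainable in intervention practices once case management is under way.

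It is also true that blinding is claimed only for the search, so the plan makes no false claim about the calls. The 18 months apply to the trial as a whole, and no schedule of searches per practice is given, so the counts above describe possible exposure, not recruitment by unblinded staff.

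A reader might want to put a size on the bias, for example by assuming a shift of 0.05 to 0.10 SD against the 0.4 SD target (0.05 / 0.4 = 12.5%; 0.10 / 0.4 = 25%). Nothing in the document supports such a shift, and it should not be used.

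A reader might also point to the provision that "Participants will be given the opportunity to discuss this issue with either their GP or trial coordinator prior to consenting" and ask for these questions to be sent elsewhere. The article does not say that this GP knows the arm, and the change would take away a reasonable opportunity for the patient.

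Finally, the article cites a review in favour of telephone reminders by clinicians, so moving calls out of the practice may cost some response. That is a real trade-off. It does not answer the core point, because the plan as written still allows allocation-aware staff to decide whom to pursue.

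**Conclusion.** The concern holds in a limited form. The plan lets a randomised practice's own staff search records under an apparent claim of blinding, and telephone non-responders with none stated. In intervention practices that blinding cannot be relied on once case management begins. Recruitment there after that time is open to allocation-aware selection, mainly through the calls.

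This rests on two inferences: that some recruitment in a practice follows its first case-managed patient, which an average of 11.5 recruits per practice makes likely, and that contact between case manager and GPs becomes known to staff who search or call. The direction and size of any bias cannot be estimated from the document. The change is worth making because such a bias could not be reliably repaired in the analysis and prevention is cheap. It is not a reason to doubt the design as a whole.

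**What to change.** In the section on patient identification and recruitment:

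1. Make the Clinical Studies Officers, kept unaware of allocation, the default for both searches and telephone calls, and state the blinding for both steps.
2. Where practice staff must do the work, require the fixed Read-code query without discretion, calls to all listed non-responders in list order, and a script that is neutral as to allocation.
3. Do not describe practice staff as blind where this cannot be kept up.
4. Report by arm the numbers searched, invited, called and consented. The article already commits to CONSORT standards for cluster trials; this names the counts that would reveal differential recruitment.

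The cost is revised wording, some transfer of work across 48 practices to a role already in the plan, and possibly a slightly lower response than calls from the patient's own practice would bring. Patients' opportunity to talk to their GP before consenting stays as it is.

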### Screening and Baseline

At the screening appointment the researcher will confirm the diagnosis of depression using the CIS-R [25]. The CIS-R is a computerised interview schedule that establishes the nature and severity of neurotic symptoms and identifies a categorical diagnosis of mild, moderate or severe depression. If the patient is depressed and meets all other inclusion criteria we will collect baseline primary and secondary outcome measures.

### Allocation

Once the baseline assessments are complete, the participant's details will be entered into our automated allocation service via telephone or the internet. Each participant will be assigned an ID number and if their practice is one assigned to collaborative care then the participant's details will be automatically sent to the relevant case manager to alert them to contact this person. All new participants' details are also sent to the trial coordinator and their GP will be informed of their involvement in the study.

## Intervention - Case Management

The experimental intervention will follow the criteria identified by Gunn et al [9] for effective quality improvement strategies, which we have developed into a collaborative care protocol, tailored to UK systems and incorporating the preferences of patients, specialists and GPs from our trial platform [17,20].

Participants will receive a structured management plan including education about depression, medication management, behavioural activation and relapse prevention. The case manager will reinforce the information given to participants by their GP and by helping participants and GPs problem solve any difficulties with medication concordance, enabling participants to make good use of their medicines. Behavioural Activation (BA) is an effective cognitive-behavioural treatment of depression [27] that focuses upon reducing avoidance and increasing activity. We found BA to be acceptable in our pilot trial [20]. Relapse prevention will involve the development of individualised recovery plans which will help participants identify signature alert symptoms to prompt them to consider reinstating both their pharmacological and psychological depression management strategies.

Scheduled patient follow-ups will be organised via six to twelve scheduled telephone and face-to-face contacts by case managers with participants over a period of fourteen weeks. After an initial face-to-face contact most other contacts will be by telephone, although the option for further face-to-face contacts will be available for participants who are having difficulty settling to telephone contact. Negotiation of contact frequency will take into account participant preference, response to treatment, the requirements of the psychosocial support programme and the amount of GP-patient contact. However, in general, contacts will be weekly for the first five weeks of contact, followed by fortnightly thereafter. The initial contact session will be 30-40 minutes with subsequent sessions 15-20 minutes each.

### Case manager training and supervision

Case Managers will be either graduate psychologists or health care qualified professionals educated through existing mental health education programmes and trained specifically to deliver the collaborative care protocol. Case managers will adhere to a clinical protocol and will be supported by specialist mental health professionals who will provide weekly supervision of cases together with advice and support. Supervision for each individual participant will be no less than four weekly and will be facilitated through a bespoke computerised patient management system (PC-MIS) [28] which automatically alerts supervisors of the need to discuss all new patients, each participant at four weekly review and those participants who are not responding to treatment.

## Control intervention - Usual GP Care

Participants allocated to the control condition will receive usual care by their general practitioner. In line with the overall pragmatic approach of the trial, we will replicate 'normal GP practice' by making no specific patient-level recommendation or requirement to alter usual care by participating in the trial. GPs will treat and refer participants as would be their normal practice and participants, irrespective of their randomisation, are able to choose whether or not to take anti-depressants or ask for referral for psychological therapy. We will record every aspect of participant's usual care.

## Outcome Parameters

### Primary outcome measure

Our primary outcome will be depression severity and symptomatology as measured by the Patient Health Questionnaire-9 (PHQ9) [29] at four months. The PHQ9 is a nine-item questionnaire, which records the core symptoms of depression.

### Secondary outcome measures

We will measure quality of life using the SF36 [30], worry and anxiety by the GAD7 [31], health care utilisation using a bespoke designed patient service utilisation questionnaire, health state utilities with the EQ5D [32] and patient satisfaction with the CSQ8 [33,34]. All measures will be taken at baseline, four and twelve months follow up (see table 1), except the CSQ-8 which will only be taken at four months. In all cases, steps will be taken to ensure that the researcher who is assessing depressive symptomatology is blind to the participant's treatment arm of the trial.

**Table 1 T1:** Outcomes and Instrument

**Outcome Parameter**	**Instrument**
**Primary Outcome**	
Depression	PHQ-9

**Secondary Outcome**	
Quality of Life	SF36
Worry and Anxiety	GAD7
Health Care Utilisation	Patient Service Utilisation questionnaire
Health State Utilities	EQ5D
Satisfaction with Care	CSQ-8

### Process Data

Process data will be collected within the trial. The extensive quantitative and qualitative work in our pilot trial has indicated that the planned intervention is effective and acceptable, and our process evaluation in this main trial will focus on (i) mechanisms of change and differential response in patient subgroups, and (ii) the process of implementation of the intervention [35]. Investigation of mechanisms of change and differential response in participant subgroups will include quantitative measurement of key participant's baseline characteristics (e.g. severity of depression; duration of depression; patient preferences; attitudes towards treatment), treatment process measures (e.g. therapeutic alliance; concordance with treatment; behavioural activity levels), contextual practice variables (e.g. anti-depressant prescription rates; availability of counselling and other mental health services) and will follow conventional procedures for analysis [36]. Investigation of the process of implementation will utilise routinely collected data from case records, session audio tapes and supervision records. The analysis will examine the implementation of collaborative care, treatment fidelity, differences between sites and different case managers and predictors of outcome.

## Analysis

### Statistical analysis of clinical data

We will analyse our primary outcome of severity of depression on the PHQ-9 at four months using between groups analysis of covariance on individual baseline depression score. Analysis will take clustering into account by use of robust standard errors in Stata. All other clinical outcome variables will be analysed as secondary variables in the same way, using least squares or ordered logistic regression as appropriate. We will analyse outcomes by site variables to detect any effects on treatment outcomes of a 'therapist effect' - differences between case managers - and practice level variables. We will investigate the effects of any missing data using imputation by best subset regression and apply CONSORT standards for cluster randomised trials [37] in data reporting.

The incremental cost per QALY of the intervention compared to the control will be calculated from NHS and Personal Social Services (PSS) perspectives following NICE evaluation guidance [38] and a wider societal perspective. The units of resource for the intervention will be collected directly and the use of other health care services by both groups will be collected through a patient questionnaire. Data on social care, other welfare services and employment details will be collected from the Patient Service Utilisation questionnaire. Intervention costs will be based on delivery costs within the trial and include supervision and appropriate capital and overhead amounts. Other unit costs will be based on long run opportunity costs and drawn from national sources. Full sensitivity analyses will be conducted with bootstrapping to provide confidence intervals around cost and effect estimates and to produce cost acceptability curves.

Qualitative data will be subject to content analysis within a qualitative methodological framework using QSR NVivo software and analysed according to the conceptual matrix of Miles and Huberman [39].

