### Recruitment of GP practices

We will recruit 48 GP practices in three different recruitment sites: Manchester, London and Bristol, each site responsible for the recruitment of 16 practices. All GP practices in the local Primary Care Trust (PCT) will be eligible for inclusion.

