### Randomisation of GP Practices

We will allocate practices by minimisation, with a random element, on centre, deprivation and practice size. We will use the Index of Multiple Deprivation 2007 [21] to assess the level of deprivation in each practice.

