## Patient Recruitment

### Sample Size

We have powered this trial to detect an effect size of 0.4. Our effect size is towards the conservative end of our platform trial confidence interval [19] SMD: 0.63; 95% CI 0.18 to 1.07, an effect size achieved by Pilling et al [22] SMD 0.42; 95% CI -0.05 to +0.89, and in line with the findings of recent reviews [23] and our group's recent meta regression [14]. An effect size of 0.4 is also regarded as the most reasonable for determining differences between interventions that are clinically meaningful [24]. Such an effect size at 90% power (alpha 0.05) would require 132 patients per group in a two armed patient randomised trial. For the proposed cluster trial, with 14 patients per cluster and the ICC found in our trial platform of 0.06, the design effect would be 1.65. The cluster trial sample size is, therefore, 440. In order to follow up 440 patients, we will recruit and randomise 550 patients to anticipate a loss to follow up of 20%.

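### The primary ANCOVA omits the three minimisation factors, so its standard error is somewhat too large if centre, deprivation and practice size are prognostic (minor)

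*Protocol article*

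**What the plan says.** Under Randomisation of GP Practices, the protocol article says: "We will allocate practices by minimisation, with a random element, on centre, deprivation and practice size". Under Statistical analysis of clinical data, it describes the primary analysis of four-month PHQ-9 as "between groups analysis of covariance on individual baseline depression score" and adds: "Analysis will take clustering into account by use of robust standard errors in Stata". The other clinical outcomes are to be handled in the same way, so the covariate choice carries over to them.

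The same section later says: "We will analyse outcomes by site variables to detect any effects on treatment outcomes of a 'therapist effect", and that sentence goes on to mention variables at practice level. Its stated purpose is to look for differences between case managers and for practice effects. It does not make centre, deprivation or practice size covariates of the primary treatment estimate, and no other section does.

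**The concern.** Minimisation deliberately balances the arms on three practice-level factors. Where those factors predict outcome, balancing them reduces the true sampling variance of the difference between arms. A model without them still counts the variation they explain as error between practices. The reported standard error then describes an allocation that ignored the factors, not the one that was carried out.

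What is at stake is precision: a confidence interval somewhat wider than it need be, a test that runs below its nominal level, and some power given up.

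**Working it through.** **Inputs from the article.** 48 practices (Recruitment of GP practices). Effect 0.4 SD, alpha 0.05, 90% power, ICC 0.06, 14 patients per cluster, 440 analysed and 550 recruited (Sample Size).

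**Assumed.** R², the share of between-practice variance explained by the three factors, is not given; I use 0 to 0.75. Some simulations also assume a baseline correlation of 0.5 and a coefficient of variation of practice size of 0.5.

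**Step 1: the plan's own figures.**
- Patients per group before clustering: 2(1.960 + 1.282)²/0.4² = 131.3, so 132. This reproduces with a two-sided alpha.
- Recruitment: 440/0.8 = 550. This reproduces.
- Design effect: 1 + 13 × 0.06 = 1.78, not 1.65; the value 1.65 follows from an ICC of 0.05. Taking 1.65 as given, 264 × 1.65 = 435.6, close to 440.
- Patients analysed per practice: 440/48 = 9.17, not 14.

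The last two discrepancies are separate matters. Below I use 440 patients in 48 practices, with 14 per practice as a sensitivity check.

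**Step 2: size of the mismatch, before baseline adjustment.** In SD² units, a practice mean has variance 0.06 + 0.94/9.17 = 0.1625. If the factors are balanced and explain a share R² of the between-practice part, the variance that matters is 0.06(1 − R²) + 0.94/9.17. At R² = 0.5 this is 0.03 + 0.1025 = 0.1325. The unadjusted standard error is then too large by √(0.1625/0.1325) = 1.107, about 11%. The true level of the nominal 5% test is 2[1 − Φ(1.96 × 1.107)] = 0.030.

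**Step 3: power at 0.4 SD.** The true standard error is √(4D/440), with D = 9.17 × the variance above. At R² = 0.5, D = 1.215 and the standard error is 0.1051, so 0.4/0.1051 = 3.81. Adjusted power is Φ(3.81 − 1.96) = 96.8%. Unadjusted power is Φ(3.81 − 1.96 × 1.107) = 94.9%.

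| R² | SE too large by | True alpha | Power, unadjusted | Power, adjusted |
|---|---|---|---|---|
| 0 | 0% | 0.050 | 93.0% | 93.0% |
| 0.10 | 1.9% | 0.046 | 93.4% | 93.9% |
| 0.25 | 5.0% | 0.040 | 93.9% | 95.0% |
| 0.50 | 10.7% | 0.030 | 94.9% | 96.8% |
| 0.75 | 17.6% | 0.021 | 95.9% | 98.1% |

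With 14 per practice, 440 patients and ICC 0.06, unadjusted and adjusted power are both 88.2% at R² = 0, then 89.6% and 91.8% at 0.25, and 91.2% and 94.9% at 0.5. That case implies about 31 practices (440/14), not the 48 planned.

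**Step 4: simulation with practices minimised.** This is a practice-level analysis with correct degrees of freedom, equal practice sizes, no baseline covariate and 4,000 trials per row. Power is shown unadjusted, then adjusted.

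| R² | Type I error, unadjusted | Power at 0.4 SD | Power at 0.3 SD |
|---|---|---|---|
| 0 | 5.0% | 91.8%, 91.0% | 71.6%, 70.5% |
| 0.10 | 4.6% | 92.8%, 92.7% | 72.0%, 72.2% |
| 0.25 | 4.1% | 92.4%, 93.2% | 72.8%, 75.0% |
| 0.50 | 3.3% | 93.4%, 95.0% | 72.0%, 78.5% |
| 0.75 | 2.8% | 94.2%, 97.8% | 73.8%, 83.4% |

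**Step 5: the planned robust-error ANCOVA, baseline correlation 0.5.**
- Equal practice sizes, R² = 0.5: mean standard error 0.105 against a true 0.098; type I error 3.4%.
- Unequal practice sizes, R² = 0.5: 0.111 against 0.102; type I error 3.4 to 3.8%.
- Unequal sizes, against a factor-adjusted random-intercept model, power at 0.3 SD: 76% and 81% at R² = 0.25; 77% and 86% at R² = 0.5.
- The same comparison at 0.4 SD under minimisation: 95.0% and 96.0% at R² = 0.25; 95.7% and 97.3% at R² = 0.5.

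**Step 6: adding the factors but keeping plain robust errors.** Type I error was about 5.2 to 8.3% across the scenarios.

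**The case against.** The strongest reply is that this hardly matters at the effect the trial is designed for. The article states: "We have powered this trial to detect an effect size of 0.4". At that effect the gain is a point or two for shares up to 0.5, and the planned test already exceeds 90% power at about 9 analysed patients per practice. Any loss also depends on how far the factors predict outcome after baseline PHQ-9 has been taken out, which the article does not report. At a share of 0.10 or less the loss is negligible. All of this stands, and it is why the point is minor.

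A second reply is that a journal article condenses the plan, and a fuller analysis plan may add design covariates. That is possible, but this is not silence: the article names a covariate and does not name the balancing factors.

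Three stronger readings are tempting and are not supported:
- **That the omission biases the result or risks a false positive.** The error goes the other way: the test is conservative, and a positive finding would stand.
- **That the trial forfeits about 9 points of power.** That gap (77% against 86%) arises at 0.3 SD with half of the between-practice variance explained. The first is not the design effect, and the document gives no support for the second.
- **That the planned robust errors are themselves too small with 48 practices.** With no prognostic factors, the planned analysis had a simulated type I error of 4.5 to 5.2%. The inflation appears only when practice-level terms are added, so it is a hazard of the remedy and not a fault in the stated model.

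**Conclusion.** The mismatch between allocation and primary model is in the text; its consequence is conditional and modest. If the three factors are prognostic at practice level, the interval is too wide and the test conservative, with type I error of about 3 to 4% at a share of 0.5.

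With 440 analysed in 48 practices and ICC 0.06, adjustment is worth about 0 to 2 points of power at 0.4 SD for shares up to 0.5, and up to about 4 points at 0.75. At 0.3 SD it is worth about 2 to 5 points at a share of 0.25 and 6 to 9 at 0.5. If the factors explain nothing, it costs about 1 point or less. These figures rest on the assumed share, near-complete balance from minimisation, and about 9 analysed patients per practice; at 14 per practice, unadjusted power falls slightly below 90% at shares of 0.25 or less.

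The change is worth making because the possible gain outweighs the possible cost, and because naming the covariates in advance closes off a later data-driven choice.

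**What to change.** State the primary model as four-month PHQ-9 on arm, baseline PHQ-9, centre, deprivation and practice size, with the form of each factor fixed before unblinded data are seen. Use the same covariates for the secondary outcomes.

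Do not simply add the factors under plain cluster-robust errors. Use either a practice random intercept with small-sample degrees of freedom (Kenward-Roger, Satterthwaite or between-within), or CR2 bias-corrected robust errors with Satterthwaite degrees of freedom.

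The cost is a short change to the analysis text, a few practice-level degrees of freedom (the exact number depends on codings that the article does not give) and a change of variance method. No new data are needed, because minimisation already requires all three factors for every practice.
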